#### Direct medical costs

The direct medical costs include outpatient costs, hospitalisation costs, and out-of-pocket expenses for healthcare medications. Outpatient costs include the reason for the visit (due to AD, AD-related symptoms, or comorbidities), the number of outpatient visits in the past 3 months, and the cost of the last clinic visit in the same 3-months period. The cost of clinic visits includes registration (general physicians or specialists), diagnostic procedures (e.g., consultation, scale evaluation), imaging (e.g., CT, MRI, SPECT, and PET), laboratory tests, medication, and non-drug treatment (such as rehabilitation treatment). The outpatient medication costs are divided into three categories: anti-dementia drugs, medications for the treatment of AD-related symptoms (e.g., sleep disorders, psychiatric symptoms, and gastrointestinal symptoms caused by medications), and the treatment of comorbidities. For anti-dementia drugs the specific medications used and their corresponding costs are also investigated. For comorbidity-associated costs, the types of comorbidity and the associated costs are recorded. Investigations into the cost of hospitalisation included the reason for hospitalisation (AD, AD-related symptoms, or comorbidities), how many times a patient was hospitalised in the past 12 months, and expenditures on the last hospitalisation within the past 12 months. The hospitalisation expenditure includes the cost of the ward bed, formal care, examinations, laboratory tests, treatment (such as rehabilitation, massage, and others), and medications. The term “self-bought medications” means that the patient or their caregivers purchased the medications outside the hospital (out-of-pocket spending). Questions include how many times medications were purchased in the past month and the total expenditure during the same period. The above data also include information regarding the patients’ payment method (including medical insurance for urban workers or town residents, rural cooperative medical insurance, commercial insurance and self-funded) and any out-of-pocket expenses.

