#### Current total number of patients with AD in China

A model is established to estimate the total number of Chinese patients with AD in 2015 based on the literature. The total number of patients with AD is defined as M and the percentage of AD patients who received anti-dementia treatment is defined as d%. Therefore, the number of anti-dementia treated patients (M_1_) is M × d%, and the number of patients not treated for dementia (M_2_) is M × (1–d)%. Based on previous reports, the percentage of AD patients who are treated for dementia is 10–30% [31, 32]. Epidemiological studies have revealed that the number of AD patients in China aged ≥ 60 years in 1990, 2000, and 2010 was 1.93 million, 3.71 million, and 5.69 million, respectively [8, 33, 34]. A linear regression model is used to estimate the age-specific prevalence of AD in 2015 by recording the prevalence of AD among different-aged patients. By multiplying the percentage of AD among elderly individuals aged ≥ 60 years by the total national elderly population (aged ≥ 60 years) in 2015, we obtain the estimated total number of AD patients of China, which is defined as M.

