#### Per capita annual cost of AD patients (who accepted or did not accept treatment)

The cost associated with treating dementia patients (F_1_) is divided into two groups: “outpatient costs” and “hospitalised or inpatient costs.” F_1_1_ is defined as the average annual cost in the inpatient group (average annual cost × the number of inpatients annually), and F_1_2_ is the average annual cost in the outpatient group (average annual cost × the number of outpatients annually). Patients described as not accepting treatment are those who did not select either “outpatient service costs” or “hospitalised costs” in their questionnaire. F_2_ is defined as the average annual cost per AD patient who did not accept treatment.

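### The national-cost formula multiplies patient counts split by anti-dementia treatment by mean costs split by outpatient or hospital use

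*Protocol article*

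**What the plan says.** Under Current total number of patients with AD in China, the article splits the national number of patients M by treatment: "the percentage of AD patients who received anti-dementia treatment is defined as d"%. M_1 is the treated share, and "the number of patients not treated for dementia (M_2_) is M × (1–d")%. The value comes from earlier reports: "the percentage of AD patients who are treated for dementia is 10–30"%.

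Under Per capita annual cost of AD patients, mean costs come from the study sample. "The cost associated with treating dementia patients (F_1_) is divided into two groups", outpatient and inpatient. The untreated group is set by questionnaire response: "Patients described as not accepting treatment are those who did not select either" outpatient or hospitalised costs. Then "F_2_ is defined as the average annual cost per AD patient who did not accept treatment".

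Under Nationwide cost due to AD, M_1 is divided 1/7 to inpatients and 6/7 to outpatients. The total is M_1_1 × F_1_1 + M_1_2 × F_1_2 + M_2 × F_2. M_2 is there relabelled as the number not accepting treatment, which is the name of the cost group, while its value is still the one derived from d.

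Under Direct medical costs, the outpatient item records "the reason for the visit (due to AD, AD-related symptoms, or comorbidities"), and the hospitalisation item records the same three reasons. Medication bought outside the hospital is a separate item.

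**The concern.** A count times a mean gives a valid stratum total only if both describe the same patients. Here they need not:

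- A patient without anti-dementia treatment who attends a clinic or is admitted for a comorbidity is counted in M_2. The questionnaire rule removes that patient from F_2 and pools the cost into F_1.
- A patient whose only treatment is an anti-dementia drug bought outside the hospital is counted in M_1 but contributes to F_2.
- Outpatient visits are asked about for the past 3 months only, so a treated patient with no recent visit or admission may also fall into F_2.

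Both strata are affected: F_2 is not the mean cost of M_2, and F_1 is not the mean cost of M_1. The national annual cost is one of the two announced main findings. The projections for 2020 to 2050 inherit the problem if they use the same unit costs.

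**Working it through.** The article states no national cost, so there is no total to reproduce. Its 1:6 ratio does give the stated 1/7 and 6/7. The share of patients priced with F_2 is 1 – d: 90% at d = 10% and 70% at d = 30%.

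**The two rules side by side**

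- Counts: treated means receiving anti-dementia treatment.
- Costs: treated means having selected outpatient or hospitalised costs.
- No text in the article equates or reconciles the two.

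**Inputs for an illustration**

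- d: 10–30% from the article; 20% is taken as a midpoint (assumed).
- R: mean annual total cost of service users divided by F_2, where the service-user mean is F_1_1/7 + 6 × F_1_2/7 (value assumed). F_1_1 and F_1_2 are read as means per patient, as the formula requires.
- s: share of all AD patients with any outpatient or inpatient cost (assumed).
- Service users are assumed to cost the same with or without anti-dementia drugs and to have the same 1:6 mix.

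**Formulas, per patient and in units of F_2**

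- As written: d × R + (1 – d) = 1 + d(R – 1)
- Consistent counts and costs: 1 + s(R – 1)
- Ratio: [1 + d(R – 1)] / [1 + s(R – 1)]

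In this model the error is zero if R = 1 or s = d.

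**Results at d = 20%, s = 50%**

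- R = 0.8: 0.96 / 0.90 = 1.07, about 7% too high
- R = 1: 1.0 / 1.0 = 1.00, no error
- R = 2: 1.2 / 1.5 = 0.80, 20% too low
- R = 3: 1.4 / 2.0 = 0.70, 30% too low

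**Varying the overlap.** Let q be the share of M_2 with some outpatient or inpatient cost, and let every M_1 patient have some. Then s = d + (1 – d)q.

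- q = 0: s = d, ratio 1.00
- q = 0.3, R = 2: 1.1 / 1.37 = 0.80 at d = 10%; 1.3 / 1.51 = 0.86 at d = 30%
- q = 0.5, R = 2: 1.1 / 1.55 = 0.71 at d = 10%; 1.3 / 1.65 = 0.79 at d = 30%

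The share of all patients counted in M_2 but excluded from F_2 is (1 – d)q. At q = 0.5 this is 0.9 × 0.5 = 45% at d = 10% and 0.7 × 0.5 = 35% at d = 30%.

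**Effect of d alone, formula as written.** Moving d from 10% to 30% changes the total by 1.3 / 1.1 = 1.18 at R = 2 and by 1.6 / 1.2 = 1.33 at R = 3.

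**The case against.** The strongest reply is that the two definitions may be closer than they look. The questionnaire is not shown, and the per-capita section does not say whether a comorbidity-only visit counts as selecting outpatient costs. The article also words d in two ways, as anti-dementia treatment and as treatment for dementia, and the second is broader. This could narrow the gap but does not close it. Visits for consultation, scale evaluation or imaging are outpatient costs without any anti-dementia drug, and self-bought medication sits outside both items whatever the reason for visits.

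Two stronger readings do not stand:

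- A reader might infer that 70–90% of patients are mispriced. That range is the size of M_2, not the share misclassified, which depends on an overlap the article does not report.
- A reader might infer that F_2 is the mean of the cheapest patients, so that the total must be too low. Total cost per patient also includes direct non-medical and indirect costs, so someone with no visit may carry heavy formal or informal care. The Discussion reports that 84.9% of patients are cared for at home by non-professionals. R above 1 is therefore an assumption. Self-buyers and patients without a recent visit who fall into F_2 also tend to lower s, which offsets an understatement.

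It is also fair to say that a condensed article may leave the base value of d, and whether it is varied, to a fuller document. That is not held against the plan. Writing the complement as (1–d)% is a notation slip whose meaning is clear from its label.

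**Conclusion.** The point holds as a mismatch of definitions fixed in the text: a main result combines counts from one classification with means from another. The national total is biased unless the two classifications coincide or the groups have the same mean total cost (in the simple model, equal shares s = d are enough).

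Neither size nor direction can be read from the article. The illustrations run from about 7% too high to 30% too low, and rest on an assumed service-use share of 50%, d = 20%, R from 0.8 to 3, and equal costs for service users with and without anti-dementia drugs. If service users cost more in total and outnumber the treated, the total is understated.

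The annual cost per patient, obtained by adding each patient's own costs, and its regression model do not use the formula and are unaffected.

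**What to change.** Use one definition for counts and costs.

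- Compute F_1 from patients with recorded anti-dementia treatment, and F_2 from patients without it, whatever other care they used.
- Split F_1 into inpatient and outpatient groups, as the formula requires, and state a rule for patients whose only treatment is self-bought, since they belong to neither group.
- Check that the case report form identifies anti-dementia drugs that are self-bought or given in hospital. The article describes recording specific drugs only for outpatient medication. For self-bought drugs it mentions the number of purchases and total spending, and for admissions only a medication cost. Where the drug cannot be identified, state the limitation and report the total under both classifications.
- Report the national total at d = 10% and 30% as well as at a stated base value, and write M_2 as M × (100 – d)%.

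Keeping the questionnaire rule and replacing d with the population share having any outpatient or inpatient cost would also be consistent, but needs a figure the article does not give.

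The cost is some recoding and a few extra runs of the formula. Some misclassification may remain for self-bought or inpatient drugs, and it cannot be assumed that no further data are needed until the form has been checked.

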#### Nationwide cost due to AD

A pilot study is performed, which reveal that the average annual ratio of inpatients to outpatients in different hospitals is ~1:6. Hence, the number of patients who undergo treatment nationwide (M_1_) is multiplied by 1/7 or 6/7 to obtain the number of hospitalised patients with AD (M_1_1_) and the number of outpatients with AD (M_1_2_), respectively. Thus, the total national annual cost of patients who accept treatment is M_1_1_ × F_1_1_ + M_1_2_ × F_1_2_. M_2_ is defined as the number of patients who did not accept treatment, and this value is multiplied by F_2_ to obtain the total annual national cost of patients who do not accept treatment. Therefore, the total annual national cost of patients with AD is M_1_1_ x F_1_1_ + M_1_2_ x F_1_2_ + M_2_ x F_2_. To estimate the costs attributable to AD, generalised linear models (GLMs) related to coexisting conditions (stroke, diabetes, heart disease, hypertension, lung disease, cancer, arthritis, and psychiatric problems) and demographics (sex, age, educational level, marital status, and household income) are used. Moreover, we estimate the total numbers of people who will be living with AD in 2020, 2030, 2040, and 2050 to predict the total annual cost of AD in future decades. Few large-scale national surveys of the monetary cost or economic burden of AD have been conducted in China, or indeed in Asia. To remedy this lack of data, we also systematically review COI studies of AD that report annual costs per patient. This will enable estimation of the proportion of the global burden of AD costs faced by China. Furthermore, it will enable comparison of the economic burden of AD in developed and developing countries.

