**Methods:**

This study planned to start in October 2015 and to finish in March 2016. It covered 30 provincial, municipal, and autonomous regions in mainland China. The sites and research centres in each region were selected randomly. The participating sites include Tier 3 hospitals, psychiatric hospitals, geriatric hospitals, nursing homes, and residences. More than 2500 patients with AD and their caregivers from all of the 81 research centres will be enrolled to fulfil the calculated sample size. The monetary costs of AD, which include direct medical costs, direct non-medical costs, and indirect costs, are being collected using the electronic medical record system and residence health system at each site; face-to-face interviews are being performed when necessary. Descriptive statistics will be used to summarise the patient characteristics and generalised linear models will be developed to calculate the costs.

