#### Calculation of costs due to AD

Different distributions will be considered for the monetary costs associated with AD, including normal, lognormal, exponential, and gamma. To compare the costs of different subgroups, *t*-tests or Kruskal-Wallis analysis of variance will be used. For base case analyses, GLMs will be developed using the gamma distribution with a log-link function [35]. Models will be developed with the total cost per person per year as the dependent variable, and independent variables will be selected using a backward selection method (*P* > 0.05 for removal), with patient age, patient sex, and MMSE severity all forced to remain in the model. Considering the diverse of research centres sites, we also added the sites as a covariant in the analysis. The variables used for backward selection will be years of formal education, time since AD diagnosis, marital status, location of residence (urban or rural), number of children, baseline MMSE score, baseline ADL score, the number of caregivers, the number of comorbidities, and caregiver demographics.

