## Discussion

To the best of our knowledge, this is the first study on AD cost that encompassed nearly all of the provincial, municipal, and autonomous regions in mainland China. To complete this survey, it is crucial to prepare a thoughtful and well-designed protocol. In the study design phase, we referred to an international popular survey method and adjusted it to China’s national conditions. We also tested the protocol in a pilot study; the results suggested that this protocol can be used in China.

This protocol includes measures specific to problems that exist in China. First, China has the largest population of any country, and the varying economic development among regions [36] might result in introduction of bias. To avoid this, the study includes 30 of the 33 provincial, municipal, and autonomous regions in mainland China. This ensures that both poor and rich areas are covered to balance the gap between them because people in poor areas may have more health problems [37]. Second, in China, hospitals with physicians for patients with AD include Tier 3 general hospitals, gerontology hospitals, mental health centres, psychiatric hospitals, and other institutions such as nursing homes, gerocomiums, and care facilities [36]. Therefore, all types of institutions are included in the current investigation to ensure representation of the diversity of AD costs among hospitals and institutions. The hospitals and institutions are selected randomly to reduce the test error. Third, the target population of this survey is patients with AD. Accurate diagnosis of AD is required for calculation of the true monetary cost of the condition. AD patients diagnosed according to the NINCDS-ADRDA criteria are enrolled in the study. In particular, to ensure accuracy, the diagnosis of patients diagnosed with AD prior to the start of this study was re-confirmed. In addition, the project team comprises a group of dementia physicians, who are trained in the diagnostic processes for dementia and AD to guarantee the quality and consistency of the diagnosis. Fourth, for accurate determination of the costs associated with AD patients, electronic records systems are used to determine the costs of all treatment items. This measure guarantees the absence of error. Therefore, the current protocol facilitates determination of the cost burden of AD patients in China.

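### The GLM is said to estimate costs attributable to AD, but with AD patients only and gross averages the plan yields the total cost of people with AD

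*Protocol article*

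**What the plan says.** Under *Nationwide cost due to AD* the article gives the purpose of its model: "To estimate the costs attributable to AD, generalised linear models (GLMs) related to coexisting conditions". It then names eight conditions and five demographic variables, household income among them.

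The statistical section, *Calculation of costs due to AD*, describes the base case: "GLMs will be developed using the gamma distribution with a log-link function". The outcome is all-cause: "Models will be developed with the total cost per person per year as the dependent variable". Three covariates are fixed, "with patient age, patient sex, and MMSE severity all forced to remain in the model", and sites are added. Comorbidity appears only among the candidates for backward selection, as a count: "the number of caregivers, the number of comorbidities, and caregiver demographics". Household income is not in that list.

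The sample consists of patients with the disease. The Discussion says "Third, the target population of this survey is patients with AD", and the abstract says "More than 2500 patients with AD and their caregivers from all of the 81 research centres will be enrolled".

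*Total cost per patient per year* adds direct medical, direct non-medical and indirect costs. The only deduction stated for ordinary living cost is 8% of basic cost for institutional care. *Direct medical costs* counts comorbidity care but also records why care was sought: "Outpatient costs include the reason for the visit (due to AD, AD-related symptoms, or comorbidities". The same three reasons are recorded for hospitalisation, and outpatient drugs are split into anti-dementia, AD-related-symptom and comorbidity categories.

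**The concern.** An attributable cost is a difference: cost with AD minus the cost that the same kind of person would incur without it. The plan names a regression as the tool for this, but the data contain only one side of the difference. Two kinds of non-AD cost then stay in a figure headed as due to AD: care for comorbidities, and the ordinary costs of being old, such as the supplements listed under *Direct non-medical costs*.

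Per-patient and national annual costs are the study's main findings, and the Conclusion offers them for national planning. A reader who takes a gross figure for an attributable one will believe that the disease costs more than the study has shown.

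**Working it through.** **1. The plan's own figures.** The article gives no attributable cost to reproduce. Its cost figures are in *Sample size*: SD 11,037 and allowable error 500. With two-sided alpha 0.05 (assumed), (1.96 × 11,037 / 500)² = 1,871.9, so 1,872 as stated. With a 25% defective rate, 1,872 / 0.75 = 2,496, or about 2,500 as stated. Both reproduce. They size the precision of a mean cost in AD patients and are not affected by this point.

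**2. Background cost is not identified.** Write the attributable cost as E(Y | AD, x) − E(Y | no AD, x). The sample informs only the first term. In a log-link model, an AD indicator equal to 1 for everyone merges with the intercept. A check with an intercept, age, comorbidity count and that indicator gave a design matrix of rank 3 with 4 columns.

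An illustration on simulated AD-only data (all values assumed) shows the consequence. A gamma model with log link was fitted to data with mean cost 11,216 (11,217 under the generating model, used below). If cost with AD is r times cost without it, the attributable share is 1 − 1/r:

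| r (assumed) | Share | Attributable cost |
|---|---|---|
| 1.5 | 33% | 3,739 |
| 3 | 67% | 7,478 |
| 10 | 90% | 10,095 |

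The data and the fit are identical in all three rows.

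**3. Comorbidity cost could be partly removed.** In the same illustration, predicting at zero comorbidities gives 8,121, or 8,121 / 11,216 = 72% of the mean, whichever row is true. That takes out the modelled comorbidity part and leaves background cost in place. The article states no such prediction, and it would be impossible if backward selection dropped the count.

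**4. The national formula does not use the model.** It multiplies the numbers of treated inpatients, treated outpatients and untreated patients by the average annual costs F_1_1, F_1_2 and F_2. These are averages of all-cause cost.

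**5. Size of the comorbidity part.** Let c be the share of direct medical cost that is for comorbidities, and m the share of total cost that is direct medical. The gross total divided by the total without comorbidity medical cost is 1/(1 − c·m). The documents give neither c nor m, so both are assumed:

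| c | m = 0.3 | m = 0.5 |
|---|---|---|
| 0.1 | 1/0.97 = 1.03 | 1/0.95 = 1.05 |
| 0.3 | 1/0.91 = 1.10 | 1/0.85 = 1.18 |
| 0.5 | 1/0.85 = 1.18 | 1/0.75 = 1.33 |

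At national level, patients with neither outpatient nor hospitalised costs enter through F_2, so comorbidity visits and admissions sit in the treated terms. The article puts treated patients at 10–30%. Assume 20% treated, treated patients costing twice as much as untreated ones, and m = 0.5 among the treated. Gross cost is then 0.2 × 2 + 0.8 × 1 = 1.2 units, and the comorbidity part is 0.2 × 2 × 0.5 × c = 0.2c. The ratio is 1.2/1.14 = 1.05 at c = 0.3 and 1.2/1.10 = 1.09 at c = 0.5. Self-bought medicines of untreated patients are ignored here.

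**The case against.** The strongest defence is that the attribution wording is confined to one sentence and two headings. Elsewhere, including the sentence that gives the national formula, the article speaks of the cost of patients with AD, which is a fair gross-cost label. That stands as a description of the text and is why the correction is mostly one of labelling. It does not remove the sentence that assigns the model a task it cannot perform.

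A reader might go further than the documents allow in four ways:

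- **That adjustment can remove no comorbidity cost.** Not so: a model with the named conditions could predict cost at none of them. The objection is that the article does not say it will.
- **That the headline figures are inflated by 1/(1 − c), hence doubled at c = 0.5.** That ratio applies to direct medical cost alone. The main findings also contain non-medical and indirect costs.
- **That the reason for every visit is on file.** The article describes visit and admission counts and the cost of the last episode. It does not describe counts or costs by reason for every episode.
- **That the planned international comparison is unsound.** This depends on whether the reviewed studies report gross or attributable cost, which the article does not say.

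The two covariate lists may also describe two separate models, and an article condenses a fuller plan. That is possible, but both sections are headed as cost due to AD and nothing tells the reader that the models differ.

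**Conclusion.** The point holds. The stated method cannot deliver the stated quantity, and neither a larger sample of the same kind nor a fuller analysis plan for these data alone would change that. What the plan yields is the total cost of people with AD.

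The comorbidity part raises the per-patient total by a factor of 1.03 to 1.33 over the assumed grid (c from 0.1 to 0.5, m of 0.3 or 0.5), with 1.18 at c = 0.5 and m = 0.3. Under the further assumptions shown, the national factor is 1.05 to 1.09. These are illustrations, not estimates. The background cost of old age comes on top, and the documents offer nothing to bound it. The conclusion on identification depends on none of the assumed values.

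**What to change.** 1. In *Nationwide cost due to AD*, delete the statement that the GLM estimates attributable cost and describe the GLM as modelling the determinants of cost. Retitle both sections, and label the per-patient and national figures as the total cost of people with AD.
2. As a secondary result, report AD-related direct medical cost from the fields in *Direct medical costs*. Classify the last visit or admission by its recorded reason, scale by the visit or admission count, and take out the comorbidity drug category. Count medication once: clinic-visit cost already contains it, so adding drug categories to AD visits would count them twice. No reason is described for self-bought medicines, so show them separately.
3. State that this secondary figure rests on the reason for the last episode and does not remove background old-age cost.
4. Reconcile the covariate lists (named conditions and household income against a removable comorbidity count without income), or say that they belong to two models. Whether to force comorbidity into the model is a choice for the authors.

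The cost is rewording plus one extra total. The fields described appear sufficient, but the authors should confirm that reason, count and cost can be linked on the case report form. No new recruitment is needed.
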